### Outcome measure

#### Primary outcome measure

The primary outcome measure is pain intensity, which will be measured by NRS. The data collector will assess pain intensity at baseline, T1, T2, and T3. Before trial, patients will be taught to use the NRS to assess the pain intensity by pointing out the appropriate number (range = 0 to 10), without having to take off the facemask, thus ensuring continued inhalation of the gas.

#### Secondary outcome measures

The following are the secondary outcomes:
Patients’ satisfaction with pain reliefPatients’ acceptance of analgesiaAdverse effectsPhysiological parameters (blood pressure, heart rate, percutaneous oxygen saturation)

Data collectors will collect data on patients’ satisfaction with pain relief, patients’ acceptance of analgesia, and adverse effects at T3. Patients’ physiological parameters will be collected at baseline, T1, T2, and T3 (Fig. 2).

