## Methods/design

### Aim

The main aim of the study is to evaluate the analgesic effect of the fixed nitrous oxide/oxygen mixture on patients with PHN. There are three secondary aims of the study:
To evaluate the safety of the fixed nitrous oxide/oxygen mixture by monitoring patients’ physiological parameters and adverse effectsTo determine the satisfaction of patients with the analgesic effect of the fixed nitrous oxide/oxygen mixtureTo investigate the acceptance of patients to the fixed nitrous oxide/oxygen mixture analgesia

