### Interventions

A clinician is responsible for assessing the patient’s condition on the ward, determining whether the patient meets the inclusion criteria, and informing the patient of the purpose of the trial, methods, possible risks, and rights of participants. Patients who meet the inclusion criteria will sign an informed consent form after agreeing to participate in the trial. The project manager will group patients who agree to participate in the trial based on the randomly assigned list and escort the patient to the treatment room, where the trial will be conducted. All patients in the trial will receive routine treatment (oral pregabalin 75 mg twice daily). Patients in the intervention group will inhale nitrous oxide/oxygen mixture with a facemask, which is a visible intervention measure. To eliminate the influence of psychological factors on the experimental results of patients in the control group, patients in the control group will inhale oxygen by a facemask. Patients in the intervention group will receive routine treatment plus a fixed nitrous oxide/oxygen mixture (contains 65% nitrous oxide and 35% oxygen), while patients in the control group will receive routine treatment plus oxygen. Before inhaling the gas, the data collector will teach the patient to use the NRS to report pain intensity. Besides, the data collector will inform patients that they have the right to stop or quit the trial at any time if they experience discomfort during the study. Before the trial begins (T0), the data collector will record the patient’s demographic and baseline characteristics; assess the patient’s pain intensity; measure heart rate, blood pressure, and percutaneous oxygen saturation; and teach the patient to inhale gas using a facemask. Patients in both groups will inhale gas using an oral-nasal mask, which is disposable and has a one-way valve. According to our previous research, the gas intake will last for 15 min [33, 34]. When the data collector opens the valve of the cylinder and the patient puts on the mask to inhale the gas, the trial will start timing. The data collector will assess the patient’s pain intensity and measure blood pressure, heart rate, and percutaneous oxygen saturation at the beginning of the trial at 5 min (T1) and 15 min (T2). To assess the patient’s pain, the data collector will ask the patient: How bad is the pain now? Patients will point to the corresponding pain score with their fingers and without having to remove the facemask. Five minutes after the end of the trial (T3), in addition to collecting the data mentioned above, the data collector will ask patients about their satisfaction with pain relief and acceptance of analgesic methods. Throughout the trial, the data collector will closely observe and ask the patient whether there are adverse effects.

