### Measurement

We will use a form to collect the baseline characteristics of patients, including age, gender, weight, height, education level, employment status, medical burden (no burden at all, basically no burden, some burden, heavy burden), location of pain, and course of the disease. Besides, the patients’ pain intensity, physiological parameters (blood pressure, heart rate, percutaneous oxygen saturation), patients’ acceptance of the analgesia, patients’ satisfaction with pain relief, and adverse effects will be recorded.

NRS will be used to assess the intensity of pain, ranging from 0 to 10, where 0 means “painless” and 10 means “worst pain imaginable” [38]. In most cases, clinicians and patients tend to use NRS to assess pain levels. Patients choose a number to represent their pain degree according to their feelings, which is easy to be understood by patients, is easy to use, and even can obtain scores in oral use, with high reliability and validity [39]. The reliability of the NRS has been proven to be moderate to high, with a maximum of 0.96. Besides, the convergence validity of NRS is 0.79 to 0.95 [40]. The patients’ physiological parameters will be monitored with an electronic sphygmomanometer (OMRON, HEM-7120) and oximeter (PC-60B). Pain intensity and the physiological parameters will be monitored simultaneously at baseline (T0), 5 min (T1), and 15 min (T2) after the trial began and at 5 min (T3) after the trial ended. Patients’ satisfaction with pain relief will be measured by a 5-point Likert scale (5, very satisfied; 4, satisfied; 3, uncertain; 2, dissatisfied; 1, very dissatisfied) [41]. The 5-point Likert scale is one of the Likert scales. Likert scale plays an important role in psychological research, which is the main method to measure attitude and personality. Besides, the Likert scale is easy to implement [42]. Furthermore, the data collectors will inquire into the patient’s acceptance of analgesia by asking the patient whether they would accept the gas inhalation to ease the pain (yes/no). Satisfaction and acceptance will be investigated at T3.

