Starting with gas inhalation, the data collectors will carefully observe and record any adverse effects on the patient. The expected adverse effects of nitrous oxide/oxygen mixture therapy include nausea, vomiting, dizziness, drowsiness, headache, hypotension, and oxygen desaturation [29]. If any adverse effects occur, the study will be terminated immediately, the patient will be given oxygen, and the adverse effects will be fully reversible in 5 min [43]. Any adverse effects concerning the intervention will be recorded throughout the trial period.

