### Statistical analysis

The test data will be analyzed by a statistical expert using SPSS version 22.0 (Chicago, IL, USA). The statistical expert is not involved in the experiment and is only responsible for the analysis of the data. We will use descriptive statistical methods to measure demographics and baseline clinical features. The difference in the primary outcome between the two groups will be examined using the *t test.* A rank sum test will be used to compare the satisfaction with pain relief between the two groups. A chi-square test will be used to analyze the patients’ acceptance of analgesia. Adverse effects will be tested by the chi-square test. Physiological parameters will be compared using the repeated measures analysis of variance. Besides the complete case analyses, multiple computations are used to replace the missing values in the resulting parameters. Data will be performed with an intention-to-treat analysis. All results are statistically significant with *p* < 0.05.

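### The planned SpO2 comparison is insensitive to brief dips and, where a reacting patient is stopped and given oxygen, is tilted towards showing no harm

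*Protocol article*

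**What the plan says.** The first secondary aim is "To evaluate the safety of the fixed nitrous oxide/oxygen mixture by monitoring" two things: physiological parameters and adverse effects.

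- **Timing of readings.** The Secondary outcome measures section says that patients' "physiological parameters will be collected at baseline, T1, T2, and T3". The Measurement section schedules SpO2, blood pressure and heart rate "at baseline (T0), 5 min (T1), and 15 min (T2) after the trial began and at 5 min (T3) after the trial ended". The Interventions section says "the gas intake will last for 15 min", so a completed session has readings at 0, 5, 15 and 20 min.
- **Analysis.** "Physiological parameters will be compared using the repeated measures analysis of variance". Adverse effects have their own chi-square test. For missing values, the Statistical analysis section plans imputation alongside complete-case analysis.
- **Gases.** The Interventions section says of the mixture that it "contains 65% nitrous oxide and 35% oxygen), while patients in the control group will receive routine treatment plus oxygen".
- **Response to a reaction.** The Measurement section lists oxygen desaturation among the expected adverse effects. On any adverse effect it halts the session at once, and then "the patient will be given oxygen, and the adverse effects will be fully reversible in 5 min". The Interventions section instead leaves it to the data collector whether to go on.
- **Recording of reactions.** The Measurement section has adverse effects observed from the start of inhalation and recorded throughout. The Secondary outcome measures section has them collected at T3.
- **Monitoring.** Participant retention and withdrawal promises close monitoring of physiological parameters but gives no frequency.

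**The concern.** For SpO2 the relevant harm is an episode: a fall in a few patients that may be short. The plan analyses arm means at fixed instants, and a mean at an instant is a poor summary of an episode.

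Two mechanisms act in the same direction. A dip that falls between readings leaves no trace in the analysed series. And if a patient who reacts is stopped and given oxygen, the later values no longer describe a patient breathing the study gas. This applies after any adverse effect, not only desaturation. A reassuring SpO2 result could then partly reflect when the readings were taken and in which patients oxygen had already been given.

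A third feature concerns interpretation. The arms breathe different oxygen fractions, so a lower mean SpO2 on the mixture may reflect 35% oxygen against oxygen and nothing more.

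**Working it through.** **The plan's own figure.** The documents give no figure for SpO2 or desaturation. The only computed figure is the sample size for pain: 2 × [(1.96 + 1.282) / (2.21 / 1.93)]² + 1.96² / 4 = 16.99, which agrees with the stated 17 per group. The plan enrols 21 per group, the number used below.

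**Step 1: chance that a reading meets an episode.** Follow-up readings fall at 5, 15 and 20 min, with gaps of 5, 10 and 5 min. Assume that onset is uniform over 0 to 20 min and that an episode lasts d minutes, with d at most 5. It overlaps a reading if it starts within d minutes before one, so the share caught is 3d / 20.

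| Duration d (assumed) | Share caught by T1, T2 or T3 | Share caught by a reading every minute |
|---|---|---|
| 0.5 min | 7.5% | 50% |
| 1 min | 15% | 100% |
| 2 min | 30% | 100% |
| 3 min | 45% | 100% |
| 5 min | 75% | 100% |

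**Step 2: effect on the comparison of means.** Assume 21 per arm, an SD of 1.5 points per reading, no episodes in the control arm, and an 8-point drop in one reading for each episode caught. With episodes in 20% of the active arm, the expected shift in the three-reading mean is 0.20 × 8 / 3 = 0.53 points if all are caught, and 0.53 × 0.30 = 0.16 if 30% are. Simulated power of a two-sided 5% test on the three-reading mean, standing in for the between-group part of the repeated measures analysis:

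| Episodes in active arm | All caught | 75% caught | 30% caught | 15% caught |
|---|---|---|---|---|
| 10% | 11% | 8% | 5% | 4% |
| 20% | 28% | 19% | 8% | 5% |
| 30% | 53% | 35% | 11% | 7% |

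The first column shows the cost of averaging alone; the others add the cost of the reading times. The simulation includes no oxygen treatment and no difference from inspired oxygen.

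**Step 3: the adverse-effect comparison.** With 21 per arm, none in control and every episode recorded, exact enumeration gives:

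| Rate in active arm | Chi-square, uncorrected | Fisher exact |
|---|---|---|
| 10% | 15% | 5% |
| 20% | 63% | 41% |
| 30% | 91% | 80% |

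**Step 4: a patient who reacts at minute 8, under the Measurement section.** Gas stops and oxygen is given. There is no on-gas value at 15 min: T2 is either missing, and so dropped or imputed, or read after oxygen. T3 follows oxygen in any case. If T3 is counted from that patient's own end of gas, it falls at the 5 min by which the protocol says the effect has reversed. Neither dropping nor imputing T2 restores the low value. Under the Interventions section the same patient might continue on gas, and T2 would then be an ordinary reading.

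**Step 5: direction of the oxygen difference.** Assuming pure oxygen and a well-fitting mask, inspired oxygen differs by up to 100 − 35 = 65 percentage points. Higher control values would widen a between-arm difference, not conceal one.

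**The case against.** The strongest objection is that the protocol has a second and better route. Desaturation is a named adverse effect, watched for from the start of inhalation and tested by chi-square. A patient can be given oxygen for desaturation only if someone noticed it, and a noticed event is recorded. A reader might infer that the trial could treat a desaturation and then report that none occurred. The documents do not support that. On the assumptions above, the adverse-effect test is also the more powerful: 63% at a 20% rate, against at most 28% for the means. This part of the objection stands and confines the point to the analysis of physiological parameters.

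Three further objections also stand:

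- A reader might take the oxygen control as a reason why dips are missed. It limits attribution; it does not hide desaturation. The stated aim also concerns the mixture as given, not nitrous oxide alone.
- The 5 min recovery time follows stopping and oxygen. It is no estimate of how long an unnoticed, untreated dip lasts, so the durations in the first table are assumptions.
- Oxygen before the next reading follows from the Measurement section only; the Interventions section leaves continuation open.

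The adverse-effect route does not fully make up for the weakness. The article states no oximetry frequency and two different collection times for adverse effects. A missing desaturation threshold may be left to the analysis plan, but no analysis plan can recover a low reading that was never written down.

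**Conclusion.** The point holds for the planned SpO2 comparison. Fixed-time means are insensitive to brief dips: 15% to 45% of episodes lasting 1 to 3 min would meet a reading. With dips in 20% of the active arm, power falls from about 28% with full capture to between 5% and 8% when 15% to 30% are caught. These figures rest on assumed rate, depth, duration, onset and SD, since the documents give none of them.

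The tilt towards no harm follows from the text, without those assumptions, wherever the Measurement section's stopping rule is applied. Its size cannot be computed from the documents.

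It would go too far to conclude that the whole safety aim fails. Noticed desaturation is captured and compared separately, and the primary outcome is unaffected.

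**What to change.** - Using the oximeter already named, record each patient's lowest observed SpO2 from gas start to T3. Include any value already displayed when gas is stopped, without delaying care to obtain one.
- Flag every reading taken after oxygen was given, and do not analyse it as an on-gas value.
- Report the change from T0 to the lowest value, and the number per arm below one SpO2 cut-off fixed before unblinding.
- Keep the between-arm SpO2 means as descriptive, with a note that they compare 35% oxygen with oxygen. The same limit on attribution applies to the lowest value.
- Reconcile the Interventions and Measurement sections on whether the session stops after an adverse effect, and the Measurement and Secondary outcome measures sections on when adverse effects are collected.

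The cost is one more entry on the form, a change of wording, and watching the oximeter throughout inhalation in both arms; the protocol does not say that the device is worn continuously or stores a minimum. The Trial status section reports 20 of 42 patients recruited, so those already treated may have only fixed-time readings. At that point 42 − 20 = 22 could still contribute the lowest value.

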**Fig. 2 Fig2:**
[figure not shown]
SPIRIT figure: schedule of enrolment, interventions, and assessments. PHN postherpetic neuralgia, T0 baseline, T1 5 min after starting the therapy, T2 15 min after starting the therapy, T3 5 min after finishing the therapy

### Data monitoring

The DMC will be set up at the same time the research project is identified. The DMC includes a pain management specialist, a chief pharmacist, a chief nurse, and a statistical specialist who chairs the DMC. During the implementation of the study, members of the DMC will review the original test data every month, check the standardization of the study, ensure the completeness and accuracy of the data, and guarantee the credibility and dependability of the study results. If the study is not performed as planned, the DMC will make corrective recommendations or stop the study. Any deviations from the trial will be recorded in the breach report form, and the study team will discuss and propose a modification plan. Update clinical trial registration information as necessary.

### Data storage

Paper material of the original test data will be stored in a locked filing cabinet in the pain department office of the General Hospital of Ningxia Medical University. All data will be input into the computer by two researchers, and access passwords will be set to keep the data secure. Personally identifiable subject information related to the data will be replaced with anonymous numbers. In order to ensure the quality of data, an independent clinical research assistant will review the original data every month to check whether the data is correct and complete. The authors will follow the guidelines recommended by the International Committee of Medical Journal Editors (ICMJE).

### Sample size calculation

We performed a pilot trial to calculate the sample size. According to our previous study on breakthrough pain [44], the sample size is calculated based on the pain intensity of patients, because the pain intensity is a primary outcome measure. Ducassé et al. [43] conducted a study on the analgesic effects of pre-mixed nitrous oxide and oxygen on patients with out-of-hospital trauma. The study confirmed that pain intensity in the intervention group (nitrous oxide/oxygen mixture) was significantly lower than that in the control group (medical air) at 5 min after administration (*p* < 0.001). Therefore, we used the pain intensity recorded at T1 as a reference in calculating the sample size. Our pilot trial involved 14 patients, with a 1:1 ratio between the intervention group and the control group. The sample size of this study was calculated by the following formula:

$$ {n}_1={n}_2=2{\left[\frac{\left({u}_{\alpha }+{u}_{\beta}\right)}{\raisebox{1ex}{$\delta $}\!\left/ \!\raisebox{-1ex}{$\sigma $}\right.}\right]}^2+\frac{1}{4}{u}_{\alpha}^2 $$where *n*_1_ and *n*_2_ represent the sample sizes of each group. ***δ*** is the difference value between the two population means. ***σ*** represents the population standard deviation. According to the pilot trial, the pain severity during the test reported by all control group patients (*n* = 7) revealed a mean (SD) of 6.71 (1.28) out of 10. Patients (*n* = 7) in the intervention group reported a mean (SD) of 4.50 (1.80). So we got *δ* = |*μ*_1_ − *μ*_2_| =2.21. The standard deviation of the entire sample (*n* = 14) was 1.93, which was ***σ*** =1.93. ***α*** represents a significance level of 5% for a two-sided test, ***u***_***α***_ = 1.96. ***β*** was the type II error, which was set to 0.1; thus, ***u***_***β***_ = 1.282. We substituted these data into the formula and calculated that *n*_1_ and *n*_2_ were 16.9. Therefore, the sample size of each group was about 17. Taking into account the 20% drop-out rate before the end of the study, we decided to enroll a total of 42 participants (21 per group).

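### The sample size formula is fed the SD of both pilot arms combined (1.93) where it needs the within-group SD (about 1.56 to 1.69), so the stated power is wrong, in the conservative direction

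*Protocol article*

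**What the plan says.** The section on sample size calculation gives a formula for comparing two means with equal groups, n = 2[(u_α + u_β)/(δ/σ)]² + u_α²/4, and says that σ "represents the population standard deviation". The inputs come from a pilot: "Our pilot trial involved 14 patients, with a 1:1 ratio between the intervention group and the control group". Control patients (7) "revealed a mean (SD) of 6.71 (1.28) out of 10". The 7 intervention patients had mean 4.50 and SD 1.80. The difference gives δ = 2.21. For σ the section does not use either arm's SD or a combination of them. It takes "The standard deviation of the entire sample" of 14, which is 1.93. The test has "a significance level of 5% for a two-sided test" (u_α = 1.96), and β "was the type II error, which was set to 0.1" (u_β = 1.282). The result is 16.9, taken as 17 per group, raised to 21 per group (42 in total) for 20% drop-out. The statistical analysis section plans a t test between the two groups for the primary outcome.

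**The concern.** In a two-mean formula, σ is the spread of scores among patients in the same group. It is the noise that the planned t test will estimate. An SD taken over both arms together also includes the distance between the two arm means. The treatment difference then enters twice: once as the signal δ, and again as part of the noise σ.

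The printed figures show that this happened. The value 1.93 is larger than both arm SDs, and a pooled within-group SD cannot exceed the larger of the two.

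What is at stake is the accuracy of the power statement for the primary outcome. Type II error 0.1, δ = 2.21 and 17 per group are presented as belonging together, and with the right σ they do not. A reader who wants to know what difference the trial was built to detect is given the wrong one.

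**Working it through.** **Inputs** (all from the sample size section): u_α = 1.96, u_β = 1.282, δ = 6.71 − 4.50 = 2.21, σ as used = 1.93, arm SDs 1.28 and 1.80, 7 patients per arm.

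**1. The plan's own figure.** 2 × (3.242 × 1.93 / 2.21)² + 1.96²/4 = 16.03 + 0.96 = 16.99, hence 17 per group. The printed 16.9 is this value cut short. Noncentral-t power with 17 per group and SD 1.93 is 89.9%. The arithmetic is sound; the fault is in the input.

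**2. What 1.93 is.** Rebuild the whole-sample SD from the arm summaries. The between-arm sum of squares is 14 × (2.21/2)² = 17.09.
- Arm SDs with divisor n − 1: the within-arm sum of squares is 6 × (1.28² + 1.80²) = 29.27. The total is 46.36, and √(46.36/13) = 1.89.
- Arm SDs with divisor n: the within-arm sum of squares is 7 × 4.878 = 34.15. The total is 51.24, and the SD is √(51.24/14) = 1.91 or √(51.24/13) = 1.99.

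The plan's 1.93 lies inside this range of 1.89 to 1.99. It is a total SD that includes the treatment difference.

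**3. The within-group SD.**
- Divisor n − 1: √((1.28² + 1.80²)/2) = 1.56.
- Divisor n, converted: 1.562 × √(7/6) = 1.69.

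**4. The same formula with the within-group SD.**
- 1.56: 2 × (3.242 × 1.562 / 2.21)² + 0.96 = 11.46, so 12 per group.
- 1.69: 2 × (3.242 × 1.687 / 2.21)² + 0.96 = 13.21, so 14 per group.

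**5. Power and detectable difference with 17 per group** (noncentral t, 32 df, two-sided 5%, noncentrality δ/(σ√(2/17))):

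| Within-group SD | Noncentrality for 2.21 | Power for 2.21 | Difference with 90% power |
|---|---|---|---|
| 1.93 (plan) | 3.34 | 89.9% | 2.21 |
| 1.69 | 3.82 | 95.9% | 1.93 |
| 1.56 | 4.13 | 97.9% | 1.79 |

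The 1.93 in the last column is a difference in points; that it equals the plan's σ is a coincidence.

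**6. Precision of the pilot SD.** On 12 df the 95% CI for 1.562 runs from 1.562 × √(12/23.34) = 1.12 to 1.562 × √(12/4.404) = 2.58. The one-sided 80% upper limit is 1.94. At an SD of 2.58 the noncentrality is 2.21/(2.58 × 0.343) = 2.50, and power with 17 per group would be about 68%.

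**7. Pilot summaries.** Seven whole-number scores give a mean of 31/7 = 4.43 or 32/7 = 4.57, never 4.50. Among whole-number sets with mean 47/7 = 6.71, the nearest SDs to 1.28 are 1.25 and 1.38 with divisor n − 1, while divisor n gives 1.278, which prints as 1.28.

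**The case against.** The best defence is that the error does no harm. It makes the trial larger than the pilot requires, not smaller. Type I error, the t test and the target of 42 are untouched, and 20 participants had already been recruited when the article was submitted. An SD from 14 patients is also so imprecise that 1.93 is a sensible planning value in size: it almost equals the one-sided 80% upper limit of 1.94. A null result would in any case be judged by its observed confidence interval, not by the planning SD.

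Most of this stands and limits the point to a correction of the power statement. It does not remove the point. The section presents 1.93 as σ itself and nowhere argues for it as a margin. Nor is the inflation a measure of uncertainty about the SD: it grows with the observed pilot difference.

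Two stronger readings are tempting and are not supported. A reader might infer from a wrong power figure that the trial is under-powered. On the pilot's own figures the opposite holds. A reader might also infer that the pilot figures contradict each other. The gap between 1.89 and 1.93 is within what divisor conventions produce, and the control SD of 1.28 is attainable with divisor n. The mean of 4.50 is impossible only if scores were whole numbers. That is the natural reading of the 0 to 10 NRS as the article describes it, but half-points are not expressly excluded, and a sum of 31.5 would give exactly 4.50. These features justify a look at the records, not a finding of error.

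**Conclusion.** The point holds as a wrong input with a conservative effect. σ = 1.93 is not the quantity the formula calls for; the pilot's within-group SD is about 1.56, or 1.69 if the arm SDs used divisor n. On those values 12 to 14 per group would meet the stated type II error of 0.1 for 2.21 points. With 17 per group, power is about 96% to 98%, and 90% power is reached for about 1.8 to 1.9 points.

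These figures assume that the printed arm means and SDs are correct, that the t test compares T1 scores as in the sample size section, and that 17 per group are evaluable. They should not be read as established power. The SD rests on 12 df, and at the upper end of its interval power for 2.21 points would fall well below 90%. For the same reason the result is no argument for recruiting fewer patients.

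**What to change.** Keep 42 patients. Recompute δ and the pooled within-group SD from the 14 raw pilot scores, state the SD divisor, and confirm whether the intervention mean of 4.50 is right and whether half-point scores were recorded. Then take one of two routes:

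- Put the within-group SD in the power statement. If the printed summaries are confirmed, for example: with a within-group SD of 1.56 (95% CI about 1.1 to 2.6, from 14 pilot patients), 17 evaluable patients per group give about 98% power for 2.21 points and 90% power for about 1.8 points. If the arm SDs used divisor n, the corresponding figures are 1.69, about 96% and about 1.9 points, with the interval recalculated.
- Keep 1.93 and 90% power, but say that 1.93 is a deliberate margin for an uncertain within-group SD and not the estimated σ, and report the estimate beside it.

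The cost is a re-check of 14 pilot records and one rewritten paragraph. Enrolment, conduct and analysis do not change.

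### The sample size formula uses the SD of the whole pilot, which contains the treatment difference, instead of the within-group SD, so 17 per group is not the number for 90% power

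*Protocol article*

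**What the plan says.** The Sample size calculation section prints a formula for comparing two means, n per group = 2[(u_α + u_β)/(δ/σ)]² + u_α²/4, and says that σ "represents the population standard deviation". The inputs come from a pilot of 14 patients, 7 per arm:

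- The control arm "revealed a mean (SD) of 6.71 (1.28) out of 10"; the intervention arm had mean 4.50 and SD 1.80. Hence δ = 2.21.
- For σ, neither arm SD is used. The value is 1.93, described as "The standard deviation of the entire sample" of 14.
- α "represents a significance level of 5% for a two-sided test", so u_α = 1.96. β "was the type II error, which was set to 0.1", so u_β = 1.282.

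The section reports 16.9, takes about 17 per group, and sets enrolment at 42 (21 per group) to allow for 20% drop-out. The Statistical analysis section plans a t test between the groups for the primary outcome.

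**The concern.** In a two-sample formula, σ is the common SD of scores within each group, because that is the error term of the t test to be applied. An SD taken over both arms together mixes two things: variation between patients on the same treatment, and the distance between the two arm means. The larger the assumed effect, the larger such an SD becomes, so δ appears in the numerator of the standardised effect and again, hidden, in its denominator. Calling σ a population SD does not resolve this, since under the design assumption there are two populations, with means δ apart.

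At stake is the statement of what the trial can detect. The pairing of 17 per group with a type II error of 0.1 is the only justification given for the trial's size. If σ is too large, the stated power is too low, and the section hides that the trial could detect a difference smaller than 2.21. That matters when a smaller observed effect has to be interpreted.

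**Working it through.** All inputs are from the Sample size calculation section: δ = 6.71 − 4.50 = 2.21; arm SDs 1.28 and 1.80 with 7 patients each; u_α = 1.96; u_β = 1.282.

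**1. The plan's figure.** With σ = 1.93:

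2 × (3.242 × 1.93 / 2.21)² + 1.96²/4 = 16.03 + 0.96 = 16.99.

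This reproduces 17 per group (the article prints 16.9). The exact two-sided 5% t-test power at 17 per group with σ = 1.93 is 89.9%. The arithmetic is sound, so the question is whether 1.93 is the right input.

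**2. What 1.93 is.** It exceeds both arm SDs, and no within-arm pooling of 1.28 and 1.80 can exceed 1.80. The SD over all 14 patients implied by the arm figures is

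√{[6 × 1.28² + 6 × 1.80² + 14 × (2.21/2)²] / 13} = √{(29.27 + 17.09) / 13} = 1.89.

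That is close to 1.93, and the text itself says the value covers the entire sample. It is a total SD. Using δ²/4 = 1.22 for the gap and 2.44 for the within-group variance, the gap makes up 1.22 / (1.22 + 2.44) = 33% of the total variance.

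**3. The SD that the formula needs.** With equal arms, the pooled within-group SD is

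√[(1.28² + 1.80²)/2] = √2.439 = 1.562.

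**4. The same formula with other values of σ.**

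| σ | Formula result | Per group |
|---|---|---|
| 1.93 (plan) | 16.99 | 17 |
| 1.562 (pooled within-group) | 11.46 | 12 |
| 1.80 (larger arm SD for both arms) | 14.91 | 15 |

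Twelve against 17 is 5 fewer per group, about 30%.

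**5. Power for δ = 2.21** (exact noncentral t, two-sided 5%):

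| Evaluable per group | σ = 1.93 | σ = 1.80 | σ = 1.562 |
|---|---|---|---|
| 12 | 76.4% | 82.0% | 91.2% |
| 17 | 89.9% | 93.5% | 97.9% |
| 21 | 95.2% | 97.3% | 99.4% |

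With σ = 1.562, the difference detectable with 90% power is 1.79 points at 17 per group and 1.60 points at 21.

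**6. Precision of the pilot.** The pooled SD of 1.562 has 12 degrees of freedom. Its 95% confidence interval is about 1.12 to 2.58, and its one-sided 80% upper limit is about 1.94. The standard error of δ is 1.562 × √(2/7) = 0.83, which gives a 95% interval of about 0.4 to 4.0.

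**The case against.** The strongest reply has four parts.

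- **The section is consistent with itself.** Given σ = 1.93, both 17 per group and 90% power follow. This stands: the fault is the choice of input, not the calculation.
- **The error is on the safe side.** A larger σ brings in more patients. Type I error and the analysis are untouched, and the Trial status section reports 20 participants already recruited. This also stands, and it is why no change to enrolment is called for.
- **Replacing 1.93 by 1.56 could give false precision.** If the true SD were 1.93, 12 per group would have only about 76% power. At the upper 95% limit of 2.58, even 17 per group would have only about 68%. This stands as a reason to show a range and not to cut the sample.
- **1.93 is a reasonable cautious value**, since it almost equals the one-sided 80% upper limit of the within-group SD. Numerically that is so, but the section does not offer 1.93 as a margin. It offers it as the σ of the formula, so the agreement is a coincidence and does not justify the text.

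The size of the discrepancy also depends on the SD chosen: with 1.80 for both arms the requirement is 15 and power at 17 is about 93%. Even that reading does not lead to 17. None of these points makes the whole-pilot SD the right quantity.

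**Conclusion.** The concern holds. The section puts a total SD where the two-sample formula and the planned t test require a within-group SD. On its own arm figures, 90% power for 2.21 points needs 12 per group, not 17. The 17 evaluable per group give about 98% power for that difference, or 90% power for about 1.8 points. At 21 per group, power is about 99%, or 90% for about 1.6 points.

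These figures assume that the printed pilot SDs are correct, that they apply to the trial population, and that the arms share a common SD. The error is conservative: on these figures the trial is not underpowered and its validity is not affected. What is wrong is the stated relation between sample size, effect and power. It should be corrected because it is the sole justification for the trial's size.

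**What to change.** In the Sample size calculation section, define σ as the common within-group SD and replace 1.93 by the pooled value, 1.56, showing how it follows from 1.28 and 1.80. Restate the result as 12 per group for 90% power at 2.21 points. Keep the 42 patients, and say that 17 evaluable per group give about 98% power for 2.21 points, or 90% power for about 1.8 points. Add that the pilot SD rests on 12 degrees of freedom, and give power over a range of SDs, for example 1.56, 1.80 and 1.93 from the table above.

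If the sponsor prefers to keep 1.93, one added sentence is enough: it is a deliberately cautious planning value, close to the one-sided 80% upper confidence limit (about 1.94) of a within-group SD of 1.56. It should then no longer be presented as the SD that the formula calls for.

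The cost is one recalculation and a few sentences. Enrolment, conduct and analysis do not change. With the first option, the text will show that the trial is larger than its stated target requires.
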